#### Follow-up booster intervention

Personalized brief MI will be delivered to each parent via WhatsApp/WeChat on a smartphone by the research nurse, who have received professional training from a clinical psychologist in delivering brief MI. The brief MI will be delivered based upon the use of a menu of strategies. The brief MI will be delivered more intensively as preferred by the parents, usually not less than once every week and not more than three times per week for the first 6 months. The frequency of delivering messages via WhatsApp/WeChat will be interactive, depending on the parents' actions and responses, their time availability as well as their progress. However, the total time spent by the interventionist would not be more than that for a traditional MI with several long sessions. After 6 months, minimal messages will be provided to the parents by merely following their progress of behavioral changes and responding to their questions to maintain contact until the 12-month follow-up.

### Ensuring intervention integrity

To ensure intervention integrity, all brief MI will be conducted by the same registered nurse via mobile instant messaging applications. The research team will periodically check the recruitment and delivery of the intervention by reviewing the messages in WhatsApp/WeChat. In addition, a weekly research team meeting will be held to evaluate the quality of intervention implementation. All brief MI sessions will be digitally recorded for review, but the subjects' personal information will remain confidential and anonymous.

### *(b) Control group*

As well as receiving usual care at the pediatric oncology outpatient clinics, like the parent-child dyads in the experimental group, those in the control group will receive the 10-min health advice session on physical activity and ask to visit the website that contains information on physical activity at the time of recruitment similar to the intervention group. However, parents will not receive brief MI throughout the study period.

### ***Outcome measures***

The primary outcome measure is the level of physical activity of the survivors at 12 months after starting the intervention. The secondary outcome measures are survivors' levels of fatigue, left- and right-HGS, PEFR and QoL at baseline, 1, 3, 6, and 12 months after starting the intervention. Participants in both groups will be required to complete the questionnaires and assessments at baseline (during their medical follow-up), 1, 3, 6 and 12 months after starting the intervention (during home visits).

### ***Measuring outcomes***

#### (1) Physical activity level

## The Chinese University of Hong Kong: Physical Activity Rating for Children and Youth (CUHK-PARCY)

The subjects' levels of physical activity will be assessed by the CUHK-PARCY. It comprises only one item adapted from two validated scales – the Jackson Activity Coding and the Godin-Shephard Activity Questionnaire Modified for Adolescents. The subjects will be asked to rate their overall weekly levels of physical activity over the past six months from 0 (no exercise at all) to 10 (vigorous exercise on most days), taking into account the frequency, duration and intensity of the activity concerned. Scores of 0-2, 3-6 and 7-10 represent low, moderate and high physical activity levels, respectively.

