### ***Subjects***

#### **a) Pediatric cancer survivors**

Hong Kong pediatric cancer survivors meeting the inclusion criteria will be invited to participate in this study. The inclusion criteria included (1) children aged from 9 to 16 years, (2) able to communicate in Cantonese and read Chinese, (3) have completed treatment for at least six months previously, (4) does not participate in physical exercise in the previous 6 months. Survivors with evidence of recurrence or secondary malignancies and those with physical impairment, cognitive impairment, or impaired mental status identified from their medical records will be excluded.

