#### In pediatric outpatient clinic

At the time of recruitment, both children and parents will receive a 10-minute health advice session on the significance of and misconceptions about regular physical activity for cancer survivors and strategies for overcoming barriers to engaging in physical activity delivered by a trained research nurse at the time of recruitment in the pediatric outpatient clinics. Parents will then receive a face-to-face brief MI session of approximately 10 minutes. In this session, parents will also be encouraged to motivate their children to intensify their physical activity levels progressively, with the ultimate goal at achieving the Global Recommendations on Physical

Activity on Health suggested by the World Health Organization. Additionally, they will be invited to visit a website from the Centre for Health Protection, Department of Health, HKSAR website (<https://www.chp.gov.hk/en/healthtopics/content/25/8804.html>) that contains information on physical activity. A comprehensive assessment will be conducted to children to identify appropriate types of physical activity for them by a research nurse who was trained by one of the coinvestigators, who is an assistant professor specializing in sports and recreation management. The assessment may involve assessing children's physical condition, for instance functional mobility, walking gait and balance. Children's preference on types of physical activity will also be discussed. All parents will be informed that they will receive an individual BMI intervention and instant messaging to facilitate the engagement in physical activity of their children via WhatsApp/WeChat on the smartphones throughout the study period.

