### **Data analysis**

The Statistical Package for Social Sciences (SPSS) software, version 25.0 for Windows (IBM Corp., Armonk NY, USA) will be used to analyze the data; all significance tests will be performed at a significance level of .05 (two-sided). Descriptive statistics will be used to calculate the mean scores, standard deviations, and score ranges of the various scales. The comparability of the two groups will be assessed using inferential statistics, including independent-samples *t*-tests and chi-squared tests. The normality of the data will be assessed using a normal probability plot and skewness statistic. Generalized estimating equation models will be used to examine the effect of the intervention on each outcome between groups over time; between-group effects, within-group (time) effects, and interaction effects (group-by-time) will be examined.

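### The six-month recall of the physical activity item reaches back before randomisation at months 1 and 3, pulling those differences, and any group effect averaged over visits, toward zero; the 12-month comparison is unaffected

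*Combined protocol and SAP*

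**What the plan says.** - **Instrument.** Physical activity is measured by one self-rated item, CUHK-PARCY, on which children "rate their overall weekly levels of physical activity over the past six months from 0 (no exercise at all) to 10" (Measuring outcomes, Physical activity level). No other recall period is given for any visit.
- **Schedule.** Both groups are to "complete the questionnaires and assessments at baseline (during their medical follow-up), 1, 3, 6 and 12 months after starting the intervention" (Outcome measures).
- **Primary endpoint.** "The primary outcome measure is the level of physical activity of the survivors at 12 months after starting the intervention" (Outcome measures). The secondary outcomes listed there at the earlier visits are fatigue, handgrip strength, peak flow and quality of life; activity is not among them.
- **Eligibility.** Criterion 4 for the child is that he or she "does not participate in physical exercise in the previous 6 months" (Subjects, a).
- **Start of intervention.** It begins in clinic at recruitment: after the health advice, "Parents will then receive a face-to-face brief MI session of approximately 10 minutes" (Intervention).
- **Analysis.** "Generalized estimating equation models will be used to examine the effect of the intervention on each outcome between groups over time" (Data analysis). Group, time and group-by-time terms are to be examined. The section does not say whether time is categorical or linear, and names no contrast as the primary test.

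**The concern.** A child who follows the instruction at month 1 must rate five months before the study and one month in it. At month 3 the split is three and three. The earlier part is inactive by eligibility, equally in both arms, so it contributes no difference between them. A real early effect would be recorded as small, and the curve over visits would look like a slow onset even if the benefit were immediate.

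Two kinds of result are exposed: the activity comparisons at months 1 and 3, and any single group effect that averages over visits. The second matters because Data analysis lists a between-group effect without tying it to month 12. An analyst following the text could judge the primary variable on an average that includes the two diluted visits.

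**Working it through.** **1. The plan's sample size.** For d = 0.5, two-sided alpha 0.05 and 80% power, the two-sample t calculation gives 64 per arm; 64/0.8 = 80 per arm, 160 in total. This matches Sample size calculation exactly. (The normal approximation gives 63 per arm, 79 after attrition, 158 in total.) The checks below use 64 completers per arm.

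**2. Share of the window after randomisation**, min(month, 6)/6:

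| Visit | Months covered | Share after | Share before |
|---|---|---|---|
| 1 | −5 to 1 | 1/6 | 5/6 (83%) |
| 3 | −3 to 3 | 3/6 | 3/6 (50%) |
| 6 | 0 to 6 | 1 | 0 |
| 12 | 6 to 12 | 1 | 0 |

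This step uses only the documents. The size of the effect below needs assumptions that are not in them: a true effect constant at 0.5 SD from day 1, a rating that averages evenly over the window, and equal (exchangeable) correlation ρ between visits.

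**3. Expected difference at each visit**, 0.5 × share, with t-test power at 64 per arm:
- month 1: 0.5 × 1/6 = 0.08 SD, power about 8%
- month 3: 0.5 × 1/2 = 0.25 SD, power about 29%
- months 6 and 12: 0.50 SD, power about 80%

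**4. Average over the four follow-up visits.** With overlap: 0.5 × (1/6 + 1/2 + 1 + 1)/4 = 0.33 SD. Without it: 0.50 SD. The SD of a four-visit mean is √((1 + 3ρ)/4).

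| ρ | SD of mean | Power without overlap | Power with overlap |
|---|---|---|---|
| 0.3 | 0.689 | 98% | 77% |
| 0.5 | 0.791 | 94% | 66% |
| 0.7 | 0.880 | 89% | 57% |

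These are t-based; the normal approximation differs by at most about one point (for example 78% in place of 77%).

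**5. Group-by-time test, categorical time, five visits.** Power depends on the sum of squares (SS) of the visit differences about their mean, with noncentrality (64/2) × SS/(1 − ρ) on 4 df.
- With overlap (0, 0.08, 0.25, 0.50, 0.50): mean 0.267, SS = 0.214. At ρ = 0.5, 32 × 0.214/0.5 = 13.7, power 86%.
- Without overlap (0, 0.50, 0.50, 0.50, 0.50): mean 0.40, SS = 0.200. At ρ = 0.5, 32 × 0.200/0.5 = 12.8, power 83%.

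The test is not weakened; the shape it describes is wrong.

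**6. Linear time.** An unweighted line through the same differences at months 0, 1, 3, 6 and 12 has slope 0.043 SD per month with overlap and 0.024 without. The fitted month-12 values are 0.59 and 0.58. Again the trajectory is distorted, not shrunk.

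**7. Months 6 and 12 only.** The average stays at 0.50 SD. With SD √((1 + ρ)/2), power is 94%, 90% and 86% at ρ = 0.3, 0.5 and 0.7, before any gain from baseline adjustment.

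**The case against.** The strongest reply is that the declared primary endpoint is activity at 12 months. Its window covers months 6 to 12, wholly after randomisation, and the sample size calculation is a simple two-group comparison that this endpoint satisfies at about 80% power. No activity endpoint is declared at months 1 or 3. All of this stands, and it limits the point to the early visits and to visit-averaged effects.

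Three stronger readings are tempting, and the documents do not support them.

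- *A reader might infer that the primary analysis is underpowered.* A 12-month contrast from a categorical-time model is not diluted. What is missing is a sentence saying that this contrast is the primary test.
- *A reader might infer that the group-by-time test is attenuated.* Steps 5 and 6 show otherwise: its power is slightly higher with the overlap, and a fitted line is steeper.
- *A reader might average all five visits and report 0.27 instead of 0.50 SD, or 49% power (ρ = 0.5) against the planned 80%.* That average includes baseline, where the expected difference is zero whatever the recall period. Even without overlap it is 0.5 × 4/5 = 0.40 SD. Like for like, the overlap moves 0.40 to 0.27 SD, and power from 83% to 49%. Nor is the planned 80% a fair comparator, since it belongs to a single two-group comparison.

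The size is also uncertain. Children may weight recent weeks more, which would reduce the dilution. A gradual build-up would make the early differences smaller still, and the plan does ask parents to encourage progressive increases in activity. Finally, the early scores have some value for handling dropout, so discarding them is not free.

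**Conclusion.** The point holds in limited form. The overlap (5/6 of the window at month 1, half at month 3) follows from the plan's own recall period and schedule, and criterion 4 fixes the direction of the bias: toward no difference. Activity estimates at months 1 and 3 cannot be read as effects at those times, and a flat early curve would be a false sign of slow onset. Under the stated assumptions, a group effect averaged over the four follow-up visits falls by a third, from 0.50 to 0.33 SD, and loses roughly 21 to 32 points of power for ρ between 0.3 and 0.7. The 12-month comparison is untouched.

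This should be fixed, but it does not invalidate the trial. It reaches the primary variable only because Data analysis leaves open which GEE term decides the result.

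**What to change.** In Data analysis, state that for physical activity the GEE takes the 6- and 12-month CUHK-PARCY scores as outcomes, with time categorical and baseline score as a covariate, and that the between-group contrast at 12 months is the primary test.

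In Outcome measures, either drop CUHK-PARCY from the 1- and 3-month visits, or keep it there for descriptive reporting with a note that the recall period overlaps the time before randomisation. If kept, the early scores may serve as auxiliary information for missing 12-month data. In either case, make no claim about activity effects at 1 or 3 months.

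The cost is about two sentences and no new data. The trial gives up early activity estimates, which are not interpretable as effects at those visits. If the scores are dropped altogether, it also gives up a little repeated-measures information for dealing with the 20% attrition that the plan allows for. The other outcomes and their visit schedule need no change on this account.

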### (2) Level of fatigue

The Chinese version of the Fatigue Scale – Child (FS-C)

The Chinese version of the FS-C will be used to assess the level of fatigue of subjects aged from 7 to 12. It consists of 14 items, evaluated on a five-point Likert Scale, with scores ranging from 14 to 70. Higher scores represent higher levels of cancer-related fatigue.

### (2) Left- and right-handgrip strength

Hand-held dynamometer (HHD) will be used to assess the survivors' right- and left-HGS. Before the measurement, the handle of the HHD will be adjusted to allow the base to rest on the first metacarpal (heel of palm) and the handle to rest on the middle of four fingers. During the test, subjects will be instructed to push as hard as they could, with their arms keeping at right angles and their elbows by the side of their bodies. The subjects will be asked to repeat the test three times with 10 to 20 seconds resting time in between each push. Only the highest of the three measurements in each subjects will be recorded.

### (4) Peak expiratory flow rates

A mini-Wright Standard Handheld peak flow meter will be used to determine survivors' PEFR. It is a useful physiological test to assess an individual's lung functionality by measuring an individual's maximum speed of expiration. It was shown to be an accurate and precise device to determine an individual's pulmonary functionality.

#### (6) Quality of life

Survivors' QoL will be assessed using the Chinese version of the Pediatric Quality of Life Inventory (PedsQL). This scale has 23 items rated on a 5-point Likert scale. These items are categorized into four domains: physical functioning (eight items), emotional functioning (five items), social functioning (five items) and school functioning (five items). Each item's score was then reverse scored and linearly transformed into a scale of 0 to 100 (0 = 100, 1 = 75, 2 = 50, 3 = 25, 4 = 0). The range of possible scores is 0–100, with higher scores representing better QoL.

#### ***Data collection***

To minimize attrition bias, intention-to-treat analysis will be used. Ethical approval will be obtained from the Institutional Review Board of the University of Hong Kong/Hospital Authority Hong Kong West Cluster and Hong Kong Children's Hospital Research Ethics Committee. Before commencement, the Chief of Service of the pediatric oncology unit will be briefed on the purpose, nature and protocol of this study. To identify potential subjects, the research assistant will approach pediatric cancer survivors who have their medical follow-ups in the pediatric outpatient clinic and ask them to indicate their willingness to participate in this study. After checking for eligibility, the research student will explain the study details, such as its nature, purpose, implications, and data collection procedure to each pediatric cancer survivors and their parents. If both the parent and the child agreed to participate, written consent will be obtained from the parents and the child's assent will be also obtained. The children and their

parents will be assured that their participation is completely voluntary and that all of the information provided will be kept confidential. The issue of confidentiality is the major ethical issue, and will be solved by recording the data in a manner that does not allow the participants to be identified (ie. using a non-recognizable code for each patient). This study will be conducted in compliance with the principle of Declaration of Helsinki and ICH-GCP.

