### ***Sample size calculation***

We used power analysis to estimate the sample size, referring to the results of our previous pilot study of the intervention and findings of our previous intervention studies on efforts to promote PA among pediatric cancer survivors in Hong Kong. An average moderate effect size (Cohen's  $d = 0.5$ ) was found for the outcomes of PA and fatigue levels, muscle strength, and QoL. Consultation with an expert panel, comprising a pediatric oncologist, a nursing specialist in pediatric oncology, and a professor and assistant professor from a local university, indicated that this result can be regarded as the minimally important difference that warrants a change in patient management. To detect a statistically meaningful between-group difference with a moderate effect size (Cohen's  $d = 0.5$ ) and a power of 80% (two-tailed; with a potential attrition rate of 20%) at  $\alpha = .05$ , a minimum of 160 parent–child dyads with 80 dyads per arm will be required.

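### Intention-to-treat does not deal with missing 12-month scores, and the GEE as described is guaranteed valid only if dropout is unrelated to earlier scores

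*Combined protocol and SAP*

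**What the plan says.** Data collection contains the only statement about bias from dropout: "To minimize attrition bias, intention-to-treat analysis will be used".

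Data analysis names the method: "Generalized estimating equation models will be used to examine the effect of the intervention on each outcome between groups over time". It adds that "between-group effects, within-group (time) effects, and interaction effects (group-by-time) will be examined". It gives no weights, imputation, working correlation, link function, missing-data assumption or sensitivity analysis.

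Sample size calculation mentions attrition once, "with a potential attrition rate of 20" per cent, and uses it only to enlarge the sample, "with 80 dyads per arm will be required".

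Outcome measures makes physical activity at 12 months the primary outcome, with assessments at baseline and at 1, 3, 6 and 12 months. Under Study design, baseline is assessed before randomisation, so every randomised dyad should have a baseline score.

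**The concern.** Intention-to-treat defines the population and keeps each dyad in its allocated arm. It says nothing about how a missing score is handled. That task falls to the model. An ordinary GEE has a general guarantee of consistency only when dropout is unrelated to the outcome, apart from what group and visit explain.

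There is reason to plan for something less benign. Under Follow-up booster intervention, parents in the intervention arm are usually messaged one to three times a week for six months about the behaviour that the primary outcome measures. Control parents receive no such contact. Families may therefore leave for different reasons in the two arms. If leaving is related to the child's activity score, and differently so by arm, the 12-month contrast can shift in either direction: towards a spurious benefit, or towards hiding a real one.

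**Working it through.** **1. The plan's own figure.** Inputs from Sample size calculation: d = 0.5, two-sided alpha 0.05, power 80%, attrition 20%.

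- Normal approximation: n per arm = 2(1.96 + 0.8416)² / 0.5² = 62.8, so 63. The t-test calculation gives 64.
- Attrition: 64 / (1 - 0.20) = 80 per arm, 160 in total. The stated size is reproduced exactly.
- With 64 completers per arm, power is about 80%. The allowance restores precision and does nothing about bias.

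**2. Bias of the 12-month difference.** The documents give no correlation or dropout model, so the following are assumptions: five visits, Gaussian outcome with SD 1, and correlation either 0.8 per visit step (autoregressive) or 0.6 (exchangeable). Dropout is monotone and reaches 20% overall by the last visit. Where it is score-related, its log-odds change by 1 per SD of the last observed score. There were 400,000 simulated subjects, a GEE saturated in group and visit, and a true effect of 0 or 0.5 SD. Ranges span both correlations and both true effects, in SD units; a positive sign favours the intervention.

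| Dropout | Independence | Exchangeable | Unstructured |
|---|---|---|---|
| Completely at random | -0.004 to 0.008 | -0.003 to 0.005 | -0.003 to 0.006 |
| Low scorers leave, same mechanism and rate in both arms | -0.001 to 0.004 | -0.003 to 0.003 | -0.001 to 0.003 |
| Low scorers leave, intervention arm only | 0.112 to 0.123 | -0.017 to 0.008 | 0.001 to 0.009 |
| Low scorers leave, intervention 30%, control 10% | 0.107 to 0.120 | -0.022 to 0.004 | 0.001 to 0.005 |
| Low scorers leave, control 30%, intervention 10% | -0.123 to -0.117 | -0.007 to 0.013 | -0.008 to -0.006 |
| Low scorers leave intervention, high scorers leave control | 0.224 to 0.234 | -0.032 to 0.010 | 0.009 to 0.014 |
| Depends on the unseen current score, intervention only | 0.132 to 0.143 | 0.040 to 0.052 | 0.050 to 0.060 |

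A separate, smaller simulation used correlation 0.5 or 0.7, dropout after month 1, no true effect and a Monte Carlo standard error of about 0.02. With dropout differing by arm, the bias was 0.04 to 0.26 SD for independence GEE, within 0.03 of zero for exchangeable GEE, and within 0.02 of zero for a likelihood model with unstructured covariance.

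**3. Non-constant variance.** Children must have done no exercise in the previous six months (Subjects), so early scores on the 0-10 rating may bunch near the floor and spread later. With SDs assumed to rise from 0.4 to 1 across visits, the exchangeable GEE was biased by 0.04 to 0.11 SD under arm-dependent dropout.

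**4. Effect on the error rate.** With 64 per arm, SE = √(2/64) = 0.177 SD. For a bias b and no true effect, the rejection probability is P(Z > 1.96 - b/SE) + P(Z < -1.96 - b/SE).

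- b = 0.1: b/SE = 0.57, giving 0.082 + 0.006 = about 8.7%.
- b = 0.2: b/SE = 1.13, giving 0.204 + 0.001 = about 20.5%.

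Relative to the design effect, 0.1/0.5 = 20% and 0.2/0.5 = 40%.

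**The case against.** The strongest reply is that a reader might infer that the GEE is valid only under completely random dropout. The calculations do not support that. With constant variance, exchangeable and unstructured GEE stayed within about 0.03 SD of zero under every arm-dependent mechanism driven by observed scores, and the bias cancelled when both arms shared mechanism and rate. This stands: what requires dropout unrelated to earlier scores is the general guarantee. But the plan fixes no working correlation, so it cannot claim the favourable case, and step 3 shows that an exchangeable structure is not a dependable rescue.

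A reader might also infer that the result will be biased towards benefit. The documents do not support a direction. Messaging could equally retain poor responders, both arms have home-visit assessments, and contact becomes minimal after six months. The table contains a case with the opposite sign.

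The plan does not say that the GEE is unweighted or uses only observed visits. That is a reading of its silence. The 20% is a potential rate, not a forecast. Dropout slopes, correlations and SD ratios are assumptions, and scores near the floor in early visits would leave less for early dropout to depend on. All of this limits the size of the problem. None of it makes intention-to-treat a remedy for missing outcomes.

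**Conclusion.** The point holds as a gap between what the plan claims and what its method secures. The protection against attrition bias stated in Data collection is not a property of intention-to-treat, and Data analysis adds nothing that provides it.

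A bias of about 0.1-0.2 SD at 12 months, with an error rate of about 9-20% in place of 5%, is conditional on two things that the documents leave open: an independence working correlation, and score-related dropout of around 20% that differs by arm. Where either is absent the bias is near zero, with the reservation about non-constant variance. Confidence is high about the omission and moderate about the size. The primary analysis should be changed, because the exposure is avoidable at little cost and concerns the primary outcome.

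**What to change.** 1. For the 12-month primary outcome, specify one of two methods.
   - A likelihood-based repeated-measures mixed model with visit as a factor, group-by-visit terms and unstructured covariance. Keep baseline as one of the responses, so that all randomised dyads enter. Restricting to dyads with a post-baseline score would narrow the promised intention-to-treat population.
   - The GEE, run on multiply imputed data for all randomised dyads, with the working correlation and link stated.
2. State that this analysis assumes data missing at random given the observed scores and group.
3. Add one delta-adjusted sensitivity analysis at 12 months, since the last row of the table shows that no working correlation protects against dropout driven by unseen scores. With 20% missing in one arm, shifting its imputed scores by delta moves the difference by 0.2 × delta, so a shift of 0.5 SD moves it by 0.10 SD.
4. Reword Data collection so that attrition bias is addressed by this method, with intention-to-treat defining only the population and the arm.

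The sample size and trial conduct do not change. The cost is analysis wording and slightly more programming. The mixed model also relies on approximate normality of a single 0-10 rating.
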